**Timetable**

Data collection for RCT baseline will begin in spring 2011 and continued through 2012 during spring and fall seasons. The seasonal variations in the subjects beginning the study in fall or spring will be different; however, during the baseline and endline measurements the weather allows similar outdoor activities.

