**The main specific purposes and hypotheses are:**

1. To test what is the effectiveness of tailored counseling to minimize inactivity periods and increase physical activity in persons involved in sitting-related work. *H: Counseling increases physical activity and decreases muscle inactivity time during workday and leisure time*
2. To test if the counseling can induce long term behavioral changes that benefit health?

*H: Counseling induces behavioral changes that last long time. Positive effects in health related markers such as serum lipids and blood pressure can be seen at 6 and 12 months after counseling.*

1. To examine what is the effectiveness of parental counseling on children’s physical activity behavior? *H: There is transfer effect of parental counseling so that also the children’s physical activity has increased.*

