**Ethics.** We will submit the study plan with questionnaires and informed consent for evaluation by the local ethics committee. The RCT will not begin before approval has been received. Subjects will be volunteers with right to withdraw from the study at any time without consequences. The study will be conducted according to good scientific practice.

**Protocol.** The protocol of the study is shown in Fig. 3. Before counseling the parents will be measured for baseline data (fasting blood samples, anthropometry, questionnaires, physical fitness test) and a representative normal day EMG activity with other measures of physical activity level. After counseling the representative day with agreed behavioral changes will be measured again using EMG and other devices for physical activity level assessment. In the first 3 months the compliance will be reinforced by phone calls and possible modifications to the agreed intervention will be made. Between 3 to 6 months the compliance will be followed once a month and no contact with the subjects will be made in the maintenance period. The midline and endline measurements include fasting measurements, questionnaires and 24-hour heart rate recordings. Control group participates only in baseline and normal day measurements, midline and endline measurements. Children will be measured at baseline, after 3, 6, 9 and 12 months for physical activity behavior using triaxial accelerometers (Actigraf).

Figure 3. Timeline of the project showing the timing of physical activity (PA) measurements for parents and children.

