**Long term main outcomes are health-related indices and maintenance of the behavioral change.** Venous blood samples for whole blood count, blood lipids and glucose analysis will be taken in standardized fasting conditions in the mornings 7-9 am. Samples will be analyzed using standard methods in clinical use and also metabonomics. Serum will be stored for later analysis of other health related markers such as glucose and lipid metabolism (leptin, obestatin, glucagon-like peptide, C-peptide). DNA-samples will be taken from volunteers and leucocytes extracted for further analysis of associations regarding body composition and physical performance and activity. Blood pressure will also be measured in the morning. Anthropometry including body composition (dual X-ray absorbtiometry and bioimpedance, In-Body 720, Korea) in fasting condition, hip-to-waist circumference and BMI will be measured. Subcutaneous fat thicknesses from several sites will be measured using ultrasonography.

Heart rate will be measured with the same device as acceleration. Both time domain (e.g. RMSSD, SDNN) and frequency domain (Ultralow frequency <0.0033 Hz, Very Low frequency 0.0033-0.04 Hz, Low frequency 0.04-0.15 Hz and High frequency 0.15-0.4 Hz) analysis of HR variation (HRV) will be performed (Tulppo et al. 2003). Histogram of heart rate will be constructed. Hyvinvointianalyysi (Firstbeat Technologies, Finland) will be used to identify the time of physical activity, MET and stress-related decreases in HRV. The variables will be compared with EMG data and MET levels calculated from questionnaires. High frequency band has special meaning in determining cardiovascular health. Heart rate will be measured at baseline (before and after counceling), at 6 and 12 months.

Behavioral changes will be assessed using questionnaires that include questions such as: TV/computer time usage, time and places/facilities outdoors both alone and with family, way of commute, time in sitting position, subjective energy level etc.

**Background variables.** Background information of medication, chronic and acute diseases will be assessed in the screening process. Dietary records for 3 weekdays and 1 weekend day will be kept at baseline, midline and endline to evaluate whether similar diet has been maintained during the year as assumed. Questions regarding perceived health and wellbeing are included in the questionnaires. Physical fitness will be assessed with non-exercise questionnaire.

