After counseling the research personnel will phone the subjects two times to ask about the compliance of the goals set and send e-mails. This reinforcement period lasts 6 months. The end measurements at 12 months are made to assess the maintenance of the habitual changes and effects on health markers. During the last 6 months there will not be researcher contact other than 9 months measurements with the subjects.

The control group will not receive the counseling intervention but will undergo the measurements similarly as the intervention group. The counseling does not include dietary counseling. The subjects will be monitored for dietary changes by questionnaires but eating habits are assumed to be maintained the same.

**Statistical analysis**. The EMG activity variables such as total inactivity time during day and mean intensity of EMG will be used to categorize people into quartiles according to 1) physical activity and 2) health marker indexes. Chi Square will be used to compare EMG distributions and levels to other variables. The difference in physiological signals between categories will be compared using One-way/Multivariate ANOVA. Correlation and regression analysis will be used to retrieve relationships between physical and health conditions and physical activity assessments. Repeated measures ANOVA will be used to determine effects of intervention complemented with mixed model ANOVA in case of missing data points.

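### Nothing ties the two arms to the same start seasons, although the children's 3- and 9-month visits fall in summer for one start group and winter for the other

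*Protocol*

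**What the plan says.** The Timetable sets the recruitment seasons: "Data collection for RCT baseline will begin in spring 2011 and continued through 2012 during spring and fall seasons". It then grants that "The seasonal variations in the subjects beginning the study in fall or spring will be different", and offers as reassurance that "during the baseline and endline measurements the weather allows similar outdoor activities". Endline is at 12 months (Measurements, Counseling intervention).

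The visits in between are set elsewhere. In Methods, Protocol: "Children will be measured at baseline, after 3, 6, 9 and 12 months for physical activity behavior". The accelerometer paragraph in Measurements repeats these months. For parents, the second hypothesis expects benefits in health markers that "can be seen at 6 and 12 months after counseling".

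On allocation, Methods, Subjects randomizes by region before recruitment and asks only that each arm contain central and suburban areas. On analysis, the Statistical analysis paragraph states: "Repeated measures ANOVA will be used to determine effects of intervention", with a mixed model where data points are missing. Neither place mentions season.

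**The concern.** The protocol identifies a seasonal difference between start groups, and its answer covers two of the five time points at which children are measured. The third hypothesis, on transfer from parent to child, rests on the children's physical activity. The counseling itself promotes family activity in places such as playgrounds, parks and forests, so weather is a plausible influence on the measurement.

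If one arm held more spring starters than the other, the arms would be compared in different seasons at 3 and 9 months. The error would change sign between those visits. It could look like an early effect that fades or a late effect that emerges, and a group-by-time test responds to that pattern. Month 3 lies in the reinforcement period and month 9 in the maintenance period, so such a pattern could easily be read as a finding about maintenance.

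**Working it through.** The protocol gives no figure for the size of seasonal variation, so there is none to reproduce. The check is calendar arithmetic followed by algebra.

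**1. Calendar.** Inputs: baseline in spring or fall (Timetable); children's visits at 0, 3, 6, 9 and 12 months (Methods, Protocol; Measurements).

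| Start | 3 mo | 6 mo | 9 mo | 12 mo |
|---|---|---|---|---|
| Spring | summer | fall | winter | spring |
| Fall | winter | spring | summer | fall |

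Only month 12 shares the baseline season. At months 3 and 9 the two start groups are in opposite seasons, summer and winter. (Methods, Design speaks of three follow-ups for children, but both detailed schedules list four, including 3 and 9 months.)

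**2. Bias in the arm contrast.** Let D be the mean summer-minus-winter difference in a child's activity, and pI and pC the shares of spring starters in the intervention and control arms. Assume that spring and fall levels are alike and that D is the same in both arms.

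- 3 months: an arm's mean is the winter level + p × D, so the contrast is off by (pI − pC) × D.
- 9 months: an arm's mean is the winter level + (1 − p) × D, so the contrast is off by −(pI − pC) × D.
- Average of the two visits: 0.
- Change from baseline to 12 months: 0, because each family is back in its own start season.
- If pI = pC: 0 at every visit.

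For illustration, pI − pC = 0.20 gives +0.2 D at 3 months and −0.2 D at 9 months.

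**3. How likely is an imbalance of that size?** Assume half of all starts are in spring.

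- Families start independently, 100 per arm: SD of (pI − pC) = √(2 × 0.25/100) = 0.07. Twenty points is then 0.20/0.07, about 2.8 SD, and unlikely by chance.
- Whole areas start in one season, k areas per arm (k is not stated): SD = √(2 × 0.25/k) = 0.50, 0.35, 0.29 and 0.22 for k = 2, 4, 6 and 10. Twenty points is then within one SD in every case.

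**4. Precision with balanced arms.** Mixing two seasons at one visit adds p(1 − p)D² to the variance, which is D²/4 at p = 0.5. In units of the within-season SD:

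- D = 0.5: 0.0625, or 6% more variance; efficiency 1/1.0625 = 0.94.
- D = 1.0: 0.25, or 25% more variance; efficiency 1/1.25 = 0.80.

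If left unadjusted, that is like losing 6% to 20% of the families at those visits. The range of D is an assumption.

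**The case against.** The strongest reply is that the trial has a concurrent control group measured in the same way as the intervention group, so season cancels unless start season differs by arm. No document shows that it does. This stands: a reader might infer that season biases the trial's results as planned, and the text does not support that. The 20-point imbalance is an assumption, plausible mainly if whole areas start in a single season, and the protocol does not say how areas will be filled over time.

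Second, the error averages out over months 3 and 9 and vanishes for change to month 12, while the children's hypothesis names no visit. This also stands. Only visit-specific contrasts and the group-by-time test are exposed.

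Third, a reader might take the weather sentence to be false or over-broad. It is not, since it speaks only of baseline and endline.

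Fourth, a reader might extend the point to the parents. Their 6-month visit falls in the other of the two seasons accepted for baseline, and the 6-month hypothesis names serum lipids and blood pressure, for which no seasonal effect is shown here. It is a minor case. The short-term EMG comparison, with counseling about one week after baseline and the repeat one week later on the same weekday, is hardly touched.

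Fifth, covariates are often left to an analysis plan, and none is shown here. The missing season term alone is therefore not a protocol error. But a later analysis plan cannot restore parallel recruitment. If few areas start in one season each, or an arm starts almost wholly in one season, adjustment has little or nothing to work with.

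**Conclusion.** The point holds in a limited form. The protocol recognizes a start-season difference, answers it for baseline versus 12 months only, and has no rule that keeps start season balanced between arms. The exposed results are the children's 3- and 9-month contrasts and the group-by-time test that includes them.

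The size is (pI − pC) × D with opposite signs at the two visits, and nil if start season is balanced. It rests on three quantities the protocol does not give: D, the imbalance, and the number of areas. The loss of precision needs no imbalance, but depends on the assumed D and on an even mix of start seasons; it is confined to those two visits and recoverable in analysis. The change is worth making because it costs very little and its main part cannot be made after enrollment.

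**What to change.** 1. In Methods, Subjects, state that intervention and control areas are recruited in parallel within each spring and fall period. The cost is advertising in both kinds of area at the same time. Control families need not be told about the intervention.
2. In Statistical analysis, or in the analysis plan, include start season and start season by visit in the repeated measures or mixed model, at least for the children's outcomes. With five visits this uses 1 + 4 = 5 degrees of freedom and only the known start dates.

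The weather sentence in the Timetable needs no change, and no measurement is added.

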### Budget

Funding for this project has been received from the Ministry of Education and Culture for 2011-2013.

### Expected research results and their practical usefulness

This research continues the PI’s project where the use of EMG to quantify physical activity level is unique. Our first results already demonstrate convincingly how little we use our muscles during normal daily life and that exercise has only limited effect on the muscle activity histograms (Finni et al. 2010ab, Haakana 2010).

As both our work and leisure time involve more sitting than ever before, the time and duration our muscles are active becomes attractive starting point for research because inactivity may induce negative effects on cellular processes in skeletal muscles or other tissues regulating risk factors like plasma triglycerides and HDL cholesterol (Hamilton et al 2007). Thus, while minimizing long periods of inactivity, we need to try to answer the question what is the frequency and duration of harmful inactivity, and vice versa, how much and how often do we need to activate our muscles or elevate HR.

The effectiveness of counseling intervention in minimizing the sitting time on muscle activity parameters will be realized in this randomized controlled study. We will also receive information if the intervention has reduced the need for occupational health care. If effective, the model of intervention can then be executed in occupational health care or through a company physician or team initiatives within work places, at homes and schools where the children benefit from this model, too. Indeed, now more than ever we must focus on children’s physical activity and inactivity. Based on social cognitive -theory (Bandura 2002) the amount of children’s physical activity and willingness to participate to different physical activities should increase if parents increase their own physical activity and take more time for physical activities with the whole family.

Therefore, the results of this study will result in information that has been especially called for in the ministry for 2007-2011: 1) Accurate and novel measure of physical activity using EMG to assess muscle activity and inactivity in addition to questionnaires, 2) Description and measure of non-exercise activity during the day in ordinary people, 3) How sitting and changes in sitting behavior can affect ordinary people’s health, fitness and non-exercise behavior and 4) Children’s physical activity behavior objectively measured by accelerometer.

**Publication plan**

This project will result in two Ph.D. theses which comprise of several original scientific articles. Most importantly, we aim that this study produces information that is relevant in various occupations from teachers to company executives. Thus, besides presenting the results at international scientific conferences and publishing in high-rank international peer-review journals we aim to write articles in the format understandable to public in various targeted magazines such as Liikunta ja Tiede, Opettaja, Taloussanomat etc. Also, the results regarding e.g. maximal inactivity periods will be published in newspapers and magazines to target the general population.

